A study in Edoret, Kenya, revealed that the overall prevalence of intimate partner violence during pregnancy was 34.1%. In this study, the prevalence of physical, sexual, and psychological intimate partner violence was 22.8% and 27.4%, respectively (Luhumyo et al., 2020). A Systematic Review and Meta-Analysis of Cross-Sectional Studies by Muluneh et al. (2020) found that the pooled prevalence of IPV among women was 44%, but the past-year IPV was 35.5%. The magnitude of psychological, physical, and sexual abuse was about 30.0%, 26.0%, and 19.0%, respectively, in the review done by Muluneh et al. (2020).

Several prevalence studies on intimate partner violence were conducted in different corners of Ethiopia (Abay Woday Tadesse et al., 2018, Adhena et al., 2020, Alebel et al., 2018, Chernet and Cherie, 2020, Tesfa et al., 2020). A study conducted in Central Ethiopia has shown that the overall prevalence of intimate partner violence among women in their lifetime and recent years is 77.0% and 62.4%, respectively (Tesfa et al., 2020). Another study conducted in Axum town, Northern Ethiopia, found that intimate partner violence during the COVID-19 pandemic was 24.6% (Gebrewahd et al., 2020). In Ethiopia, a systematic review and meta-analysis by Alebel et al. (2018) showed that the prevalence of intimate partner violence during pregnancy was 26.1%. It is somewhat lower than individual empirical studies done in different parts of Ethiopia. Chernet and Cherie (2020) found nearly similar rates of intimate partner violence among women in Ethiopia.

A recent cross-sectional study by Adhena et al. (2020) established that the overall prevalence of intimate partner violence during pregnancy was 37.5%. But variations in the prevalence of psychological (25.1%), sexual (17.7%), and physical (13.4%) intimate partner violence during pregnancy were observed (Adhena et al., 2020). Furthermore, the prevalence of domestic violence was 64.6%. This study revealed that physical, psychological, and sexual intimate partner violence were 44.1%, 39.1%, and 23.7%, respectively (Yohannes et al., 2019). A study conducted among 612 pregnant women revealed that the prevalence of at least one type of intimate partner violence during the recent pregnancy was 59.0%. Separately, the prevalence of psychological and emotional violence, sexual violence, and physical violence was 33.0%, 36.3%, and 20.3%, respectively (Lencha et al., 2019).

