**5.3.2 Specific Objectives**

1. To assess the prevalence and associated factors of IPV during pregnancy
2. To explore the community's perspectives of IPV during pregnancy
3. To evaluate the effect of couple-based violence prevention education on couples knowledge, attitudes, and controlling behavior towards IPV during pregnancy
4. To compare the effect of couple-based violence prevention education on the experience of IPV during pregnancy
5. To compare the effect of couple-based violence prevention education on women’s autonomy and self-efficacy

1. **Methods and Materials**

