**Secondary outcome variables**

- Knowledge, attitudes, and control towards IPV during pregnancy
- Knowledge: Good versus Poor Knowledge,
- Attitude: supportive versus not supportive attitude toward IPV
- Controlling behavior: yes versus no
- Women’s autonomy and self-efficacy

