**Emotional/psychological violence: a** pregnant mother will be asked the following three psychological violence questions: (i) “say or do something to humiliate her in front of another person”, (ii) "threat to hurt or harm her or someone she cares about,” and (iii) insult or make her feel bad about herself” in the last 12 months and during the most recent pregnancy (Abramsky et al., 2011). If the mother responds to one of these emotional or psychological IPV questions, it will be recorded as 1 = yes; otherwise, 0=no (she has not experienced any emotional or psychological intimate partner violence during this pregnancy).

**Social support: The** Oslo-3 Social Support Scale (OSSS-3) will be used to measure the social support of women. The OSSS-3 consists of three items assessing the level of social support among women. Pregnant women will be asked, **Oslo 1**: How many people are so close to you that you can count on them if you have great personal problems? The responses will be: 1. 'None, 2. ‘1–2’ 3. ‘3–5’ 4, ‘5+’; **Oslo 2:** How much interest and concern do people show in what you do? The responses will be "none."2 ‘little’ 3 ‘uncertain’ 4 ‘some’ 5 ‘a lot’ and **Oslo 3**: How easy is it to get practical help from neighbors if you should need it? The response will be 'very difficult. 2 ‘difficult’ 3 ‘possible’ 4 ‘easy’ 5'very easy. The sum scores range from 3 to 14. Then the sum scores will be categorized as 3–8 (**poor social support**), 9–11 (moderate**social support),** and 12–14 (strong**social support**).

**Knowledge of IPV:** couples will be asked about nine items of knowledge questions on IPV. Couples who scored about 75% or above of the correct answer will be scored as “good knowledge,” and those who scored less than 75% will be scored as “poor knowledge (Oche et al., 2020).

**Attitude towards IPV**: To measure attitude toward intimate partner violence during pregnancy, couples will be asked, “In your opinion, is a husband justified in hitting or beating his wife in the following situations?" (a) “If she goes out without telling him?” (b) “If she neglects the children?” (c) “If she argues with him?” (d) “If she refuses to have sex with him?” (e) “If she burns the food?” Responses of “supportive attitude toward IPVp” to one or more of the scenarios were coded 1; “not supportive attitude toward IPVp" to all scenarios was coded '0'. (Trott et al., 2017).

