| 605 | Forcing partner to have sex when he/she does not want to is sexual violence | | | | Yes………………………………….1  No…………………………………..2 | | | | | | | | | | | | | | |  | | |
| 606 | Forcing partner to do something sexual that he/she finds degrading or humiliating is sexual violence | | | | Yes………………………………….1  No………………………..………….2 | | | | | | | | | | | | | | |  | | |
| 607 | Belittling or humiliating a partner in front of other people is psychological violence | | | | Yes……………………………….….1  No…………………………………...2 | | | | | | | | | | | | | | |  | | |
| 608 | Intimate partner violence during pregnancy has adverse maternal and newborn outcomes | | | | Yes…………………………….…….1  No…………………………………...2 | | | | | | | | | | | | | | |  | | |
| 609 | Intimate partner violence is human right violation | | | | Yes……………………………….….1  No…………………………………...2 | | | | | | | | | | | | | | |  | | |
| 610 | **Attitude** | | | | | | | | | | | | | | | | | | |  | | |
| 611 | In your opinion, is a husband justified in hitting or beating his wife in the following situation   1. Yes 2. No | | | | | |  | | | | | | | | | | | | |  | | |
| 612 | If she goes out without telling him? | | | | | | 1 | | | | | | | | | | 2 | | |  | | |
| 613 | If she neglects the children? | | | | | | 1 | | | | | | | | | | 2 | | |  |  |  |
| 614 | If she argues with him? | | | | | | 1 | | | | | | | | | | 2 | | |  |  |  |
| 615 | If she refuses to have sex with him? | | | | | | 1 | | | | | | | | | | 2 | | |  |  |  |
| 616 | If she burns the food? | | | | | | 1 | | | | | | | | | | 2 | | |  |  |  |
| 617 | **Controlling behavior** | | | | | | | | | | | | | | | | | | |  |  |  |
|  | In your opinion, is the husband is justified in controlling you in the following situation?   1. Yes 2. No | | | | | | | | | | | | | | | | | | |  |  |  |
| 618 | Jealous if she talked with other men | | | | | | 1 | | | | | | 2 | | | | | | |  | | |
| 619 | Accused her of unfaithfulness | | | | | | 1 | | | | | | 2 | | | | | | |  |  |  |
| 620 | Did not permit her to meet her friends | | | | | | 1 | | | | | | 2 | | | | | | |  | | |
| 621 | Tried to limit her contact with family | | | | | | 1 | | | | | | 2 | | | | | | |  |  |  |
| 622 | insisted on knowing where she is | | | | | | 1 | | | | | 2 | | | | | | | |  | | |
| 623 | did not trust her with money | | | | | | 1 | | | | | 2 | | | | | | | |  |  |  |

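### The secondary outcome labelled attitude to intimate partner violence during pregnancy asks only whether wife-beating is justified, with no reference to pregnancy, so the attitude part of objective 3 is not measured as worded

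*Protocol*

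**What the plan says.** Specific objective 3 (section 5.3.2) is "To evaluate the effect of couple-based violence prevention education on couples knowledge, attitudes, and controlling behavior towards IPV during pregnancy". The list of secondary outcomes in section 6.6.1 opens with a bullet of the same scope, "Knowledge, attitudes, and control towards IPV during pregnancy", but the line that defines the variable is wider: "Attitude: supportive versus not supportive attitude toward IPV".

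Section 6.17 returns to pregnancy: "To measure attitude toward intimate partner violence during pregnancy, couples will be asked, “In your opinion, is a husband justified in hitting or beating". Five situations are then put to the respondent. These are going out without telling him, neglecting the children, arguing, refusing sex and burning the food. The scoring rule is "Responses of “supportive attitude toward IPVp” to one or more of the scenarios were coded 1", and rejection of all of them is coded 0 under the matching label.

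The women's questionnaire (Annex II, Part Six) uses the stem "In your opinion, is a husband justified in hitting or beating his wife in the following situation". The husbands' form (Annex III) has the same stem, and the Amharic versions (Annexes VI and VII) say the same. The operational definition of intimate partner violence (section 5.10) covers physical, psychological and sexual violence, alone or combined.

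**The concern.** An outcome can support only the claim that its items ask about. Here the name and the code labels carry two qualifiers that the items lack: a time (during pregnancy) and a scope (all forms of violence). Against the named construct, a respondent could be placed wrongly in either direction. A husband who would justify beating in general, but not while his wife is pregnant, is coded as supportive. One who rejects beating but accepts forced sex or humiliation is coded as not supportive.

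At stake is how one specific objective is reported. Followed as written, the plan would present a difference, or its absence, in general acceptance of wife-beating as an effect, or no effect, on attitude to violence during pregnancy.

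**Working it through.** No figure in the plan depends on this point, so the check sets the named construct beside the items.

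| Place | Pregnancy named? | Form of violence |
|---|---|---|
| Objective 3 (5.3.2) | Yes | IPV, unrestricted |
| 6.6.1, opening bullet | Yes | IPV, unrestricted |
| 6.6.1, variable line | No | IPV, unrestricted |
| 6.17, introduction and code labels | Yes | IPV, unrestricted |
| 6.17, question and situations | No | Hitting or beating |
| Annex II, items 612–616 | No | Hitting or beating |
| Annex III, items 211–215 | No | Hitting or beating |
| Annex VI, items 611–615 (Amharic) | No | Hitting |
| Annex VII, items 410–414 (Amharic) | No | Hitting |

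1. **Timing.** No stem or situation refers to pregnancy, in either language, and no other attitude item fills the gap. The forms do name pregnancy elsewhere: women's item 608 on maternal and newborn outcomes, husbands' item 203, and the stems of the section on experienced violence.

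2. **Form of violence.** Refusing sex appears as a reason for beating. It does not ask whether forcing sex is acceptable. Nothing in the attitude items asks about sexual or psychological violence as the act.

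3. **Could pregnancy be implied because the couples are pregnant?** Baseline is at 10 to 12 weeks (6.15.1) and endline follows after 8 months (6.2).
   - 8 × 52/12 = 34.7 weeks.
   - 10 + 34.7 = 44.7 and 12 + 34.7 = 46.7, so about 45 to 47 weeks from the start of gestation.
   - Counting instead from the last session (33 to 36 weeks) plus two months (2 × 52/12 = 8.7 weeks) gives 41.7 to 44.7 weeks.

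   On either count most women will have delivered, taking about 40 weeks as term (my assumption; the protocol gives no figure). Section 6.5 also requires residence until two months after birth. So the implied context is pregnancy at baseline and the postpartum period at endline. The before-and-after McNemar comparison within each arm (6.24, data processing and analysis) would then be labelled as a change in attitude to violence in pregnancy, when neither wave asked about it.

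**The case against.** The best defence is that general wording is a reasonable choice. The protocol's literature review lists attitudes supportive of wife-beating among the risk factors for intimate partner violence, and says that risk factors in pregnancy closely resemble those in general. Section 6.17 cites a published source for the coding (its content cannot be checked here), and general items keep comparability with other studies. The variable line in section 6.6.1 already omits pregnancy. Some non-physical coercion is also covered, because the questionnaires ask separately whether a husband is justified in controlling his wife, scored as its own outcome.

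Most of this stands, and it supports keeping the items. It does not support the label. An established item set still measures what its words ask. The line in section 6.6.1 shows that the protocol uses two names for one outcome, and even the shorter one is wider than hitting or beating. The controlling-behaviour items do not reach forced sex or humiliation.

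A reader might infer three stronger points that the documents do not support.

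- *That the intervention is mainly about pregnancy, so the attitude most likely to change is missed.* In Table 2 and the manual's session schedule, only session 2 centres on consequences of violence in pregnancy. The rest is largely definitions, gender norms, relationships, power, and communication. The manual's session steps carry more pregnancy content, but also cover power, triggers and empowerment. The five situations fit much of that material.
- *That the items cover the least common form of violence.* The study used for the sample size does report "psychological (25.1%), sexual (17.7%), and physical (13.4%) intimate partner violence during pregnancy were observed". But those are rates of experienced violence, not of attitudes, and another study in the same section has physical violence as the most common form (44.1%, against 39.1% psychological and 23.7% sexual).
- *That the trial as a whole cannot support its conclusions.* See the verdict.

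**Conclusion.** The point holds as a mismatch between label and measure in one secondary outcome. The attitude part of objective 3, as worded, is not measured. What is measured is general acceptance of wife-beating.

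It goes no further than that. The primary outcome, experience of intimate partner violence, does not use these items. The randomised comparison of general acceptance of wife-beating is valid as it stands, since both arms get the same questions at the same times. The protocol states an objective and an outcome label rather than a conclusion, so the error can be corrected before anything is reported.

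The share of respondents whose code would differ under a pregnancy-specific question, or one covering all forms of violence, cannot be derived from the protocol, and I attach no number to it. The verdict rests on the wording of the items alone. The statement about endline timing also rests on the stated schedule being kept and on the 40-week assumption.

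**What to change.** In objective 3, section 6.6.1 and section 6.17, rename the attitude outcome *attitude justifying wife-beating (physical violence, not pregnancy-specific)*. Relabel the codes to match: 1 for justifying it in at least one situation, 0 for none. Limit the interpretation to that construct. No item, analysis or sample size changes. The cost is a few lines of protocol text and a narrower claim.

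Optionally, if a pregnancy-specific claim is wanted, add *while she is pregnant* to the stem in all four forms before baseline and keep it unchanged at both waves in both arms. This costs some comparability with studies that use the general wording. Because most women will have delivered by endline, the phrase would describe a current state at baseline and a past or hypothetical one at endline, which the report should say. It would not widen the form of violence, so the name should still say physical violence.

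In the same edit, correct the English husbands' form, which lists going out without telling him twice (items 211 and 212) and omits burning the food, so it does not match section 6.17 or the other three forms.

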**Controlling behavior**: couples will be asked six questions: (i) “jealous if she talked with other men”, (ii) ”accused her of unfaithfulness”, (iii) “did not permit her to meet her friends,(iv) “tried to limit her contact with family,(v) “insisted on knowing where she is, and “did not trust her with money(Antai, 2011). Couples responded “yes” to one or more of the control questions coded as 1. Otherwise, it will be coded 'no as 0.

**Women’s autonomy**: women's decision-making Autonomy will be assessed by asking couples who decide on household purchases, including small and large ones, and who decides on visiting relatives and friends. Who decides how to spend the wife's earnings? Who decides the number of children to have? And who decides to obtain health care for themselves? The response options will be “husband only’’, wife only’’ or ‘’both husband and wife”. Women will be considered to participate in decision-making if they make decisions alone or jointly with their husbands. A composite measure will be created using the sums of equally weighted binary input variables. Women will be scored one (1) for answers to each variable that included her (alone or jointly) in decision-making; otherwise, they will be scored zero (0). The index of household decision-making power (autonomy) contains five variables; thus, the respondents will be scored from 0 to 5. Two binary measures from these indexes will be created to indicate women with higher versus lower autonomy. The high and low categories will be created by dividing the sample indexes into approximately half, in which those who score below the mean score are considered to have low autonomy or lower involvement in household decision-making, and those who score above the mean score are considered to have higher decision-making autonomy or higher involvement in household decision-making (Uthman et al., 2009).

**Women’s Self-Efficacy: The** Generalized Self-Efficacy Scale (GSES), which was developed by Albert Bandura, will be used. The General Self-Efficiency Scale (GSES) consists of 10 items scored on a 4-point Likert scale, from 1 (not at all true) to 4 (exactly true). The total scale ranges from 10 to 40, with higher self-efficacy (score of ≥20) and lower self-efficacy (score of <20) (Liping Peng et al., 2020).

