| 108 | What is your ethnicity? | | | Hadiya..................................................................1  Kembata...............................................................2  Silte......................................................................3  Amhara.................................................................4  Others, specify.....................................................5 | | | | | | | | | | | | | | | | |  | |
| 109 | What is your husband’s ethnicity | | | Hadiya..................................................................1  Kembata...............................................................2  Silte......................................................................3  Amhara................................................................4  Others, specify.....................................................5 | | | | | | | | | | | | | | | | |  | |
| 110 | What is your education level? | | | No education.........................................................1  Attended elementary school(1-8).........................2  Attended high school(9-12)………………….….3  Attended college or higher(tertiary)education…..4 | | | | | | | | | | | | | | | | |  | |
| 111 | What is your husband’s education level? | | | No education.........................................................1  Attended elementary school(1-8).........................2  Attended high school(9-12)……………………..3  Attended college or higher(tertiary)education…..4 | | | | | | | | | | | | | | | | |  | |
| 112 | What is your occupation? | | | Housewife.............................................................1  Government employee..........................................2  Self-employed ……………………………..........3  Others, specify......................................................4 | | | | | | | | | | | | | | | | |  | |
| 113 | What is your husband’s occupation? | | | Farmer ..................................................................1  Government employee........................................2  Self-employed ……………………………..........3  Others, specify......................................................4 | | | | | | | | | | | | | | | | |  | |
| 114 | What is your average family monthly income in Birr? | | | Birr per month(estimate of the respondent)  ……………………………. | | | | | | | | | | | | | | | | |  | |
| 115 | Does your husband currently smoke cigarete? | | | Yes………………...………………………….....1  No………………...………………………….......2 | | | | | | | | | | | | | | | | |  | |

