|  | Who makes Final decisions in your household activities :  1. wife alone  2. Respondent and husband together  3. Husband alone  4. someone else | | | |  | | | | | | | | | | | | | | |  | | |
| 501 | On household purchases including small and large ones? | | | | 1 | | | | 2 | | | | | 3 | | | | 4 | |  | | |
| 502 | Visiting relatives and friends? | | | | 1 | | | | 2 | | | | | 3 | | | | 4 | |  | | |
| 503 | Spending the wife's earnings? | | | | 1 | | | | 2 | | | | | 3 | | | | 4 | |  | | |
| 504 | The number of children to have? | | | | 1 | | | | 2 | | | | | 3 | | | | 4 | |  | | |
| 505 | Obtaining health care for you? | | | | 1 | | | | 2 | | | | | 3 | | | | 4 | |  | | |
| 506 | **SOCIAL SUPPORT** | | | | | | | | | | | | | | | | | | |  | | |
| 507 | How many people are so close to you that you can count on them if you have great personal problems? | | | | None...................................................1  1–2.....................................................2  3–5.....................................................3  5+......................................................4 | | | | | | | | | | | | | | |  | | |
| 508 | How much interest and concern do people show in what you do? | | | | none…………………………………1  little………………………..………...2  uncertain…………….........…………3  some………………….……………..4  a lot………………….………………5 | | | | | | | | | | | | | | |  | | |
| 509 | How easy is it to get practical help from neighbors if you should need it? | | | | very difficult …...………………..…1  difficult…………..…………………2  possible…………………..…………3  Easy…………………….………..…4  very easy…..….…………….………5 | | | | | | | | | | | | | | |  | | |
|  | **PART SIX: KNOWLEDGE, ATTITUDE AND CONTROLLING BEHAVIOUR QUESTIONS** | | | | | | | | | | | | | | | | | | |  | | |
| 600 | **Knowledge** | | | | | | | | | | | | | | | | | | |  | | |
| 601 | Have you heard of Intimate partner violence? | | | | 1. Yes 2. No | | | | | | | | | | | | | | |  | | |
| 602 | Media, hospitals, health center are examples of sources of information for intimate partner violence | | | | Yes ----------------------------------1  No -----------------------------------2 | | | | | | | | | | | | | | |  | | |
| 603 | IPV is a serious public health issue | | | | Yes ………………………………….1  No …………………………………..2 | | | | | | | | | | | | | | |  | | |
| 604 | Slapping, kicking, dragging, beating, choking, pushing, etc., are examples of IPV | | | | Yes…………………………………..1  No …………………………………..2 | | | | | | | | | | | | | | |  | | |

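### The autonomy index scores a say over the wife's earnings without a no-earnings code, so the item is undefined for women who earn nothing and the score partly reflects earning status

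*Protocol*

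**What the plan says.** Under Women's autonomy, section 6.17 lists five household decisions, among them "Who decides how to spend the wife's earnings". On the answers it says "The response options will be “husband only’’, wife only’’ or ‘’both husband and wife". The woman scores 1 "for answers to each variable that included her (alone or jointly) in decision-making; otherwise, they will be scored zero (0"). The index "contains five variables; thus, the respondents will be scored from 0 to 5". It is then cut at the sample mean: "those who score below the mean score are considered to have low autonomy", and those above the mean have higher autonomy.

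In Annex II, Part Five, the item is number 503, "Spending the wife's earnings". The codes are wife alone, both together, husband alone and "4. someone else". There is no code for having no earnings and no skip. The Amharic form (Annex VI) has no such code either. The form does skip questions that do not apply elsewhere, for example at items 202, 302 and 402.

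Item 112 of Annex II, "What is your occupation", lists housewife as its first code. Section 6.9 says the kebeles are rural. Women's autonomy is a secondary outcome (6.6.1) and part of specific objective 5.

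**The concern.** A woman with no earnings has no decision to take about spending them. The form gives her two ways through. Her answer may leave her out (husband, someone else or blank), and the rule then gives her the same 0 as an earner whose husband controls her money. Or she may answer for a situation that does not exist, and the answer wife or together earns a point. Neither measures autonomy.

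Take two women. Wife A has no earnings and shares in all four decisions open to her. Wife B earns, shares in the same four and has no say over her own money. If A's item is scored 0, both score 4.

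Three things are at stake:
- The score mixes earning status with autonomy. Section 1.2 lists being a housewife among the predictors of violence in pregnancy, so the admixture may be related to the primary outcome.
- Where the item is always 0, it cannot register a change.
- Where it is answered hypothetically, the answer may depend on what the couple has been taught. A take-home exercise in the Annex V handout asks who decides on the same five matters, and the handout advises couples to decide about money together. Control couples get none of this from the research team (6.15.1).

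**Working it through.** **The plan's own range.** Five 0/1 items sum to 0 to 5, as stated. With item 503 fixed at 0 the range is 0 to 4. If a woman without earnings answers wife or together, she can reach 5.

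**Assumptions (none is in the documents).** p is the average chance of a say per item, 0.6 to 0.8. h is the share of women without earnings, 0.3 to 0.9. A woman's own chance varies around p by a beta distribution with parameters 4p and 4(1-p). Both groups have the same true say.

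**Formulas.** An earner's score is beta-binomial over 5 items. With item 503 at 0, a non-earner's score is beta-binomial over 4 items. The sample mean is (1-h) x 5p + h x 4p = p(5 - h). High autonomy means a score above that mean.

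| p | h | Mean | Score needed for high | High, earners | High, non-earners | Gap (points) |
|---|---|---|---|---|---|---|
| 0.6 | 0.3 to 0.9 | 2.82 to 2.46 | 3 or more | 63.8% | 50.4% | 13 |
| 0.7 | 0.3, 0.6 | 3.29, 3.08 | 4 or more | 56.4% | 35.3% | 21 |
| 0.7 | 0.9 | 2.87 | 3 or more | 76.5% | 64.4% | 12 |
| 0.8 | 0.3 to 0.9 | 3.76 to 3.28 | 4 or more | 72.2% | 51.6% | 21 |

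**Varying the zero.** If non-earners answer wife or together at half the true rate, the gap is about 7 to 11 points (for example 56.4% against 45.8% at p = 0.7). If they answer at the same rate as earners, it is 0.

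**Varying the correlation.** If a woman's five answers are independent, the gap with item 503 at 0 is larger. Classed low, non-earners against earners: 52.5% - 31.7% = 21 points at p = 0.6; 76.0% - 47.2% = 29 at p = 0.7 (34.8% - 16.3% = 19 when h = 0.9); 59.0% - 26.3% = 33 at p = 0.8.

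**Effect on a difference in mean score.** Suppose the intervention raises every item by d. Earners gain 5d and non-earners, with item 503 stuck at 0, gain 4d. The average gain is (5 - h)d, a loss of h/5: 0.3/5 = 6% to 0.9/5 = 18%. This also needs every non-earner to score 0.

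**Wife A.** She scores 4, and the largest mean in the table is 0.8 x (5 - 0.3) = 3.76, so she is classed high throughout. A non-earner with 4 points becomes low only if the mean exceeds 4, for example at p = 0.9 and h = 0.3: 0.9 x 4.7 = 4.23.

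**The case against.** The protocol nowhere says that a woman without earnings is to be scored 0. A reader might infer that she can never exceed 4 of 5, but with no other code she must choose among the listed answers, and together gives her the point. Nor is a fully participating non-earner necessarily pushed into the low group: she stays high in every case tabulated. Both objections stand. So does a third, that housewife does not mean no income, so item 112 cannot supply the affected share.

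A reader might also infer a biased comparison between arms. The documents do not support that. Both arms use the same form at both surveys, and randomisation makes the flaw equal on average at baseline. Occupation is collected and baseline characteristics are compared. A chance imbalance in earning status is possible with 16 clusters, and the taught material could shift hypothetical answers in one arm at endline, but neither is demonstrated. A rise in apparent autonomy among women who start earning between surveys is likewise only a possibility.

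The protocol plans a pilot in 27 couples (6.16) and reliability and validity tests that name autonomy (6.22). These might bring the problem to light, but they leave the scoring rule as written. The five-item index comes from a cited source whose handling of non-earners cannot be seen here. That is a reason to keep it for comparison, not to leave the item undefined.

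**Conclusion.** The point holds as a measurement flaw in one secondary outcome. Item 503 is undefined for women without earnings, and the rule the protocol itself fixes turns their answers into either an automatic 0 or a hypothetical point. The score therefore partly reflects earning status.

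The gap in high autonomy is about 12 to 21 percentage points if all such women score 0, under the assumed participation, share without earnings and within-woman correlation. It is larger if answers are independent, smaller as more non-earners answer wife or together, and nil if they answer as earners do. The true size cannot be told from the documents. The primary outcome, the sample size and the randomisation are not affected. The change is worth making because it is cheap.

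**What to change.** Either of two changes would do.

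1. Add a code for no own earnings / not applicable to item 503 in Annex II and Annex VI. In 6.17, define autonomy as the share of applicable decisions taken alone or jointly (denominator 4 or 5). This share should be analysed as a mean, because a mean split of fourths and fifths leaves a rounding artefact: at p = 0.7 in the model above, 64.4% of non-earners but 56.4% of earners lie above the common mean.
2. Use items 501, 502, 504 and 505 for all women and report item 503 among earners only. This treats both groups alike even with a mean split, and the score needs no new data. Restricting item 503 to earners does need a record of who earns, which occupation supplies only roughly.

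The cost is one response code and one sentence, or one sentence alone. The downside is that the score is no longer identical to the cited five-item index. Keep that index as a sensitivity analysis.
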